### Sample size and statistical analyses

We hypothesise that SPPC positively influences the QOL of the caring parents. The null hypothesis is that QOL does not differ between parents of patients in the SPPC programme and the comparison group. The sample size (number of paediatric patients) was calculated to be able to show a difference of 1 point in the QOLLTI-F score [27] 1 month after study inclusion. The calculations are based on an expected mean QOLLTI-F of 5.5 (on a scale from 0 to 10) and an expected standard deviation of the QOLLTI-F score of 1.7, as reported in Cohen et al. [27]. Note that similar values of mean ± SD, i.e., 5.8 ± 1, were observed by Groh et al. [36].

Sample size was calculated using a resampling method. Each sample size, n i = 1,...,41 = 10, ..., 250, was evaluated by simulating *R* = 499 times the QOLLTI-F of n_i_ individual pairs of care giving parents from a multivariate normal distribution, using a correlation of 0.8 between parents of the same patient. For each sample size n_i_, half of the patients were allocated to the SPPC group and comparison group, with mean QOLLTI-F of 6 and 5, respectively, and a (within group) standard deviation of 1.7. Assuming that only one parent participates in the study for 30% of the patients, this proportion of simulated QOLLTI-F scores for the second parent was omitted, resulting in simulated QOLLTI-F scores for a pair of parents for 70% of the patients, and for only one parent for the remaining 30% of patients. The difference in QOLLTI-F between parents of SPPC vs. comparison patients was then estimated with a linear mixed-effects model with group (SPPC vs. comparison) as fixed factor, modelling a random intercept per patient (to account for the non-independence of parents from the same patient). Sample size was set to ensure at least a power, 1 – β, of 0.8 at a significance level, α, of 0.05.

For this study, a total of 98 paediatric patients should be recruited (i.e., 49 from the SPPC programme and 49 for comparison) to ensure a total of 98 evaluable pairs of care giving parents, considering a drop-out rate (i.e., proportion of patients who died or withdrew informed consent before QOLLTI-F could be assessed at least once) of 10%. Sample size was estimated using R (Version 3.5.0) [37], using the R packages nlme [38] and sse [39].

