#### Primary and secondary analyses

The primary outcome QOLLTI-F of the care-giving parents 1 month after study inclusion will be analysed by a linear mixed-effects model with QOLLTI-F at baseline and group (SPPC vs. comparison) as fixed effects. A random intercept will be modelled per patient (to account for the non-independence of parents from the same patient). In addition, all measurements of QOLLTI-F taken at different follow-up visits will be analysed by a linear mixed-effects model as above, but with an additional random intercept per parent (to additionally account for the non-independence of multiple measurements per parent).

To adjust the effect size estimate for SPPC vs. comparison for potential confounders, we will use propensity score weighting. Potential confounders were already identified and include characteristics of the patient (diagnosis, age, sex), disease duration, family system (sense of coherence, family hardiness), sociodemographic variables of the family (e.g. parental living situation, family income), and contextual information (e.g. study site characteristics). As a sensitivity analysis, we will add the most important confounders as covariates in the statistical models (analysis of covariance approach).

Secondary endpoints will be analysed by linear mixed-effects models or generalised linear mixed-effects models (in case of non-normal error distribution). Normal linear models or generalised linear models may be used for secondary outcomes measured only once per patient. Sensitivity analyses will be performed as applicable and appropriate.

Missing measurements of the primary outcome, QOLLTI-F at 1 month, will be multiply imputed, based on measurements taken at 2 weeks (first follow-up measurement) and available patient characteristics.

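### The imputation rule for the 1-month QOLLTI-F does not name study group or baseline score; followed as written, it pulls the estimated SPPC effect toward zero

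*Protocol article*

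**What the plan says.** The protocol article, Primary and secondary analyses, analyses the 1-month QOLLTI-F by a "linear mixed-effects model with QOLLTI-F at baseline and group (SPPC vs. comparison) as fixed effects", with a random intercept per patient because two parents of one child are not independent. The rule for missing data follows in the same section. For parents without a score at that visit, the values "will be multiply imputed, based on measurements taken at 2 weeks (first follow-up measurement) and available patient characteristics".

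That section also lists the confounders for the propensity score. There, patient characteristics are glossed as diagnosis, age and sex. Disease duration, family system, family sociodemographics and study-site context are listed as separate items. Under Intervention and comparison, group is determined by the recruiting site.

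On deaths, Sample size and statistical analyses defines drop-out as the "proportion of patients who died or withdrew informed consent before QOLLTI-F could be assessed at least once". Outcomes and procedures ends care-phase follow-up when the child dies, and Table 2 marks QOLLTI-F at care timepoints only.

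**The concern.** An imputation model should contain at least the variables of the analysis model it feeds. Here the named predictors are the 2-week score and patient characteristics. Neither group nor baseline score is a 2-week measurement, and in the article's own usage neither is a patient characteristic.

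If group is absent from the imputation model, a parent in the SPPC group and a parent in the comparison group with the same 2-week score receive values from the same distribution. The imputed part of the data then carries only as much of the group difference as the 2-week score already shows. The primary estimate becomes a blend of the true difference among observed parents and a smaller one among imputed parents.

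The drop-out allowance does not remove the issue. It covers only families lost before any QOLLTI-F assessment, so a family with a baseline score but no 1-month score falls to the imputation rule. Participants who fail to complete questionnaires may be withdrawn, after which no data are collected. Some parents without a 1-month score can therefore be expected to lack the 2-week score too.

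**Working it through.** **The plan's own sample size.** Inputs from Sample size and statistical analyses: "a difference of 1 point in the QOLLTI-F score"; "a (within group) standard deviation of 1.7"; "using a correlation of 0.8 between parents of the same patient"; one parent only for 30% of patients; equal groups; power 0.80; α 0.05, taken as two-sided because sidedness is not stated; drop-out 10%.

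- Information per patient: 0.7/(1.7² × (1 + 0.8)/2) + 0.3/1.7² = 0.7/2.601 + 0.3/2.89 = 0.269 + 0.104 = 0.373.
- Effective SD per patient: √(1/0.373) = 1.64 (1.6375 before rounding).
- A noncentral-t calculation with this SD needs 44 per group (power 0.808), or 88 patients. 88/0.9 = 97.8, rounded up to 98.

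The stated 98 reproduces, and the imputation rule does not enter it.

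**Size of the shrinkage by hand.** Let m be the fraction missing at 1 month, e the group difference at 2 weeks and r the correlation between one parent's scores at two visits. Take equal groups, no average difference at baseline, values missing at random by family and a true 1-month difference of 1.0. Without group in the imputation model, the imputed difference is s × e, where s is the pooled slope of the 1-month on the 2-week score:

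s = (r × 1.7² + 0.25 × e) / (1.7² + 0.25 × e²), and estimate = (1 − m) × 1.0 + m × s × e.

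- If the 2-week score is also missing, or e = 0, the imputed difference is 0 and the estimate is 1 − m: 0.90, 0.80 and 0.70 for m = 10%, 20% and 30%.
- If e = 1 and the 2-week score is observed, with r = 0.5: s = (1.445 + 0.25)/3.14 = 0.540, giving 0.954, 0.908 and 0.862.
- Same, with r = 0.7: s = (2.023 + 0.25)/3.14 = 0.724, giving 0.972, 0.945 and 0.917.

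**Simulation.** 200,000 families per scenario, SD 1.7, parent correlation 0.8, 70% pairs, 1-month scores missing at random by family, and regression on baseline and group. Varied: r of 0.5 and 0.7; e of 0, 0.5 and 1; and 0%, 50% or 100% of missing parents also lacking the 2-week score. Patient characteristics and propensity weights were not simulated. Range of the estimate over scenarios (true value 1.0):

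| Missing at 1 month | Imputed from 2-week score | 2-week score + baseline | 2-week score + baseline + group |
|---|---|---|---|
| 10% | 0.89–0.97 | 0.89–0.95 | 0.98–1.01 |
| 20% | 0.79–0.95 | 0.79–0.90 | 0.99–1.01 |
| 30% | 0.68–0.92 | 0.69–0.85 | 0.98–1.01 |

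The simulation agrees with the hand formula up to simulation error. The middle column shows that adding baseline without group leaves the shrinkage in place. The co-parent's score was not tested separately.

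**Illustration for power.** Hold the standard error at 1.6375 × √(2/44) = 0.349 and use Φ(effect/0.349 − 1.96). Power is 0.82 at an effect of 1.0, 0.78 at 0.95, 0.73 at 0.90, 0.63 at 0.80 and 0.52 at 0.70. The unchanged standard error is a simplification.

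**The case against.** The strongest reply is that the sentence gives a basis for imputation and not a closed list. The article condenses a fuller protocol, and an analysis plan may well add the analysis-model variables. The 2-week measurements could also be read to include the co-parent's 2-week score. This stands in part: one can say that group and baseline are not named, not that they are excluded. But the article does not leave the matter open. It states a rule for the primary outcome, and an analyst applying that rule would build a model without group.

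Second, the effect may be modest. This also stands. With 10% missing, the 2-week score observed and the full effect present by then, the estimate is 0.95–0.97. The 10% drop-out figure is not a 1-month missing rate, so it fixes neither a low nor a high value.

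Third, the planned mixed model of all follow-up QOLLTI-F scores contains group and baseline, and no imputation is stated for it. It is a useful check and could reveal a discrepancy, but it targets all visits and does not repair the primary estimate.

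A reader might also infer that the plan creates carer scores for bereaved parents, because the rule states no exception for death. The document does not say so. Care-phase follow-up ends at death and no QOLLTI-F is scheduled afterwards, so such a score can equally be read as not due. What can be said is that the handling is unspecified.

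**Conclusion.** The point holds for the omission of group. Followed as written, the rule attenuates a true 1.0-point effect to about 0.89–0.97, 0.79–0.95 or 0.68–0.92 with 10%, 20% or 30% missing. The shrinkage is close to the full missing fraction when the 2-week score is also missing or shows no effect yet, and smaller otherwise. These figures rest on assumed missing rates, visit correlations, 2-week effects and values missing at random, none of which the article gives.

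Two stronger readings are not supported. One is that the missing baseline and co-parent scores each add to the bias: adding baseline alone changes little, and the co-parent's score is expected mainly to affect precision and the within-family correlation. The other is that a number of early deaths, or a direction of bias from them, can be worked out. The life expectancy of less than 6–12 months under Participants and recruitment is one of six indication criteria, not a median survival for the study population. Deaths before 1 month remain a secondary point about which parents the primary estimate describes.

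**What to change.** State that the imputation model for the 1-month QOLLTI-F includes at least group, baseline QOLLTI-F, the 2-week score, the patient-level clustering (for example through the co-parent's score) and the propensity-score variables.

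As a secondary clarification, state whether parents of children who die before 1 month are imputed, and report deaths before 1 month by group. Whether to restrict the target to parents of children alive at 1 month is a choice of estimand for the study team, not a correction that follows from the document.

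The cost is a few sentences, settled before the analysis, and slightly more programming. All the variables are already scheduled for collection, and the target of 98 patients does not change.

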### Data management, monitoring and risks

The sponsor-investigator is implementing and maintaining quality assurance and quality control systems to ensure that the study is conducted and data are generated, documented (record), and reported in compliance with the protocol, good clinical practice, and applicable regulatory requirement(s). Data extracted from the patient charts will be entered into an internet-based secure data base secuTrial® developed in agreement to the Good Clinical Practice guidelines provided by the Clinical Trials Centre Zurich. Person data will be pseudonomised through secuTrial®. Local coordinators will be assigned to assist with and facilitate logistics concerning the availability of medical charts and workspace in each participating study site. Data collectors will receive instructions and training before the start of data collection to assure and enhance data quality. Furthermore about 5% of the charts will be randomly chosen and data will be collected by two different people for quality checking.

A quality assurance audit/inspection of this study may be conducted by the competent ethics committee. The quality assurance auditor/inspector will have access to all medical records, the investigator’s study related files and correspondence, and the informed consent documentation that is relevant to this clinical study. We consider the risk for participants in this study as minimal. Allocation to intervention and comparison groups is determined by the natural environment of the four study sites’ care services.

## Discussion

This study evaluates the effectiveness of SPPC and its impact on patient-, family-, health professional-, and healthcare-related outcomes. The study will contribute to current knowledge by providing relevant outcome data based on the assessment of SPPC services within a comparative effectiveness research framework. Reporting on outcome metrics at the family level and providing detailed contextual information on healthcare provision has the potential to guide the expansion and sustainability of services and improve the quality of care for children with life-limiting conditions and their families internationally.

Determining clinical effectiveness will require prospective studies using comparison groups to establish the relationship between the receipt of SPPC and selected outcomes on the client and service levels [23]. However, the classical randomised controlled trial study design with its origin in establishing the efficacy of new drugs under controlled situations falls short in evaluating the effectiveness of a complex intervention in a real-world setting. Effectiveness research broadens the design options for evaluating interventions by possibly loosening up some of the rigorous control measures mandatory in a randomised controlled trial and therefore trading off strong internal validity in favour of generalisability (external validity) [40]. The consequence of less rigorous controls is an increased risk of confounding, which may limit causal interpretation of the study results.

Dealing with potential imbalance between intervention and comparison group will likely be this study’s greatest challenge. We will take all possible and reasonable measures, e.g. propensity scoring, multilevel modelling to ensure justified group comparisons and interpretation. The study’s rich longitudinal data over a period of approximately 1 year will allow a unique reporting on courses of illness of the child, of the QOL of close family members and the family’s financial hardships.

A variety of outcome indicators were used to assess the impact of SPPC so far. Widger et al. found 82 different indicators reported through 46 studies. Among this large number, indicators such as location of death, length of stay in hospital and number of hospital admissions, only 22 indicators were reported in at least two studies [41]. Many of these so far used indicators are also assessed in our study. Others, such as our main outcome of QOL on different levels are less investigated, limiting comparability with our study results.

The main results of this study will be communicated to patients, their family, and the involved healthcare professionals by a letter in lay language. The study group will make every endeavour to publish the data in peer-reviewed journals and we are convinced that this study’s comparative effectiveness and longitudinal approach will generate new meaningful evidence to advance the field of PPC internationally.

## Data Availability

Not applicable.

## Abbreviations

DCGM: DISABKIDS Chronic Generic Measure
FHI: Family Hardiness Index
FSOC: Family Sense of Coherence
HCP: Health Care Professional
MSAS: Memorial Symptom Assessment Scale
QOL: Quality of Life
QOLLTI-F: Quality of Life in Life Threatening Illness–Family Carer
PaPaS-Scale: Paediatric Palliative Screening Scale
PC: Palliative Care
PPC: Paediatric Palliative Care
ProQOL: Professional QOL
SPPC: Specialised Paediatric Palliative Care
WHOQOL: The WHO Quality of Life
WüTi: Würzburger Trauerinventar
